##### The severity grading of PONV

The severity will be self-assessed using the scores from the visual analog scale (VAS) at pre-operation, postoperative 8 h, 24 h, and 48 h. VAS allows patients to rate the intensity of their symptoms (scored 0, none; scored 1~3, mild; scored 4~6, moderate; scored 7~10, severe).

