##### Quality of life

The quality of life will be self-administered using the functional assessment of the SF-12 questionnaire at pre-operation, postoperative 24 h and 48 h. The SF-12 questionnaire measures 12 items, which can be classified as a physical and mental component [25].

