##### Blood tests

Blood samples will be collected at pre-operation and postoperative 24 h to measure the levels of serological indicators. The fasting venous blood will be drawn and centrifuged, the separated serum is stored at a – 80 °C refrigerator. Gastric secrete elements and 5-hydroxytryptamine will be analyzed in the research laboratory of Beijing North Biotechnology every week.

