### Statistical methods

#### Statistical methods for primary and secondary outcomes {20a}

The efficacy and safety analysis will be conducted according to the intention-to-treat principle. As the third party, the statistical analysis will be performed by the Institute of Clinical Basic Medicine, China Academy of Chinese Medical Sciences, using the statistical packages of social sciences software (SPSS; version 19.0). All the results are based on two-sided tests. Continuous data will be presented as means and standard deviations and compared using the independent *t* test or Wilcoxon’s rank-sum test. On the other hand, categorical data will be presented as percentages and frequencies and analyzed using the chi-square or Fisher’s exact test. The missing values will be implemented by the method of multiple imputations. A *p* value less than or equal to 0.05 will be considered statistically significant.

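### One p ≤ 0.05 significance label covers primary and secondary outcomes alike, so an isolated secondary result could carry a confirmatory label it has not earned

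*Protocol article*

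**What the plan says.** Section {20a} of the protocol article gives one set of rules for primary and secondary outcomes. On sidedness: "All the results are based on two-sided tests". Continuous data are to be "compared using the independent *t* test or Wilcoxon’s rank-sum test", and categorical data go to a chi-square or Fisher's exact test. The section then sets the threshold: "A *p* value less than or equal to 0.05 will be considered statistically significant". It names no repeated-measures model, no adjustment for the pre-operative value and no time point of main interest. It does not distinguish the standing of a primary p value from that of a secondary one.

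The schedule of the secondary outcomes is in section {12}:

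- Symptom severity on the VAS: "The severity will be self-assessed using the scores from the visual analog scale (VAS) at pre-operation, postoperative 8 h, 24 h, and 48 h".
- SF-12 schedule: "The quality of life will be self-administered using the functional assessment of the SF-12 questionnaire at pre-operation, postoperative 24 h and 48 h". According to the article, the items can be grouped into a physical and a mental component.
- Blood tests, before surgery and at 24 h: "Gastric secrete elements and 5-hydroxytryptamine will be analyzed in the research laboratory". The number of gastric measures is not given.

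The Objectives section {7} states a single confirmatory hypothesis, AHP against APP, in terms of an effect that is not tied to a named variable. The sample size section {14} is based on the primary endpoint.

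**The concern.** The point rests on what {20a} fixes, not only on what it leaves out. A secondary p value at or below 0.05 earns the same label as the primary one. With several outcomes measured at several visits, and only two-group tests offered, an ineffective plaster has a good chance of producing at least one result that the rule calls statistically significant, such as VAS at 8 h alone or one SF-12 component at 48 h alone. Nothing in the article says that such a result is supportive only, so it could be reported as evidence of efficacy. The 5% attached to it would hold for that single test, not for the set from which it was picked.

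**Working it through.** The article states no error rate for the secondary set, so there is no figure to reproduce. The calculation shows what the stated rule implies.

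**Inputs from the article**

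- Per-test threshold: two-sided 0.05 ({20a}), that is 0.025 in the direction of benefit.
- Post-operative comparisons ({12}): VAS at 8, 24 and 48 h = 3; SF-12, 2 components × 2 visits (24 and 48 h) = 4; serum at 24 h, at least one gastric measure plus 5-hydroxytryptamine = at least 2. Total k = 3 + 4 + 2 = 9.
- The Abstract's wording on severity would also allow nausea and vomiting to be scored separately. That adds 3 VAS comparisons and gives k = 12.

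**Assumptions**

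- Each comparison is tested separately (inferred, not stated).
- There is no true difference on any secondary outcome (global null).
- The correlation ρ between test statistics is not given. It is taken as equal for all pairs, with 0 to 0.7 as the working range and 0.9 as an extreme.

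**Step 1, independent tests (ρ = 0)**

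- Either direction: 1 − 0.95^9 = 0.370; for k = 12, 1 − 0.95^12 = 0.460.
- Benefit only: 1 − 0.975^9 = 0.204; for k = 12, 1 − 0.975^12 = 0.262.

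**Step 2, correlated tests.** For k equally correlated standard normal statistics, this is the probability that at least one has |z| > 1.96 (either direction) or z > 1.96 (benefit only):

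| Tests | Direction | ρ = 0 | ρ = 0.5 | ρ = 0.7 | ρ = 0.9 |
|---|---|---|---|---|---|
| 9 | either | 37% | 27% | 20% | 12% |
| 9 | benefit only | 20% | 13% | 10% | 6% |
| 12 | either | 46% | 32% | 23% | 13% |
| 12 | benefit only | 26% | 16% | 12% | 7% |
| 3 (VAS alone) | either | 14% | 13% | 11% | 8% |

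**Step 3, a more realistic correlation pattern.** Repeated scores on one outcome should correlate more strongly than scores on different outcomes. With nine tests, ρ of 0.5 within an outcome and 0.3 between outcomes gives 31% in either direction and 16% for benefit. With 0.8 and 0.5, the figures are 25% and 12.5%. Both pairs lie inside the ranges for equal correlation.

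**Reading.** For nine tests and ρ from 0.7 to 0, the either-direction rate is 20% to 37%, about 4 to 7 times the nominal 5%. The false-benefit rate is 10% to 20%, about 4 to 8 times the nominal 2.5%.

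**The case against.** The strongest reply is that this is an omission of a kind the article may leave out. A testing order, a main time point and the status of secondary p values are commonly set in an analysis plan, which is not shown. The 0.05 sentence is the usual per-test convention and does not claim control over a family of tests. The outcomes are labelled secondary, only one confirmatory hypothesis is stated, and the sample size rests on the primary endpoint. Unadjusted secondary tests are common practice where no confirmatory claim hangs on them.

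Much of this stands. The absence of a hierarchy is not an error, and a gatekept key secondary outcome is a preference. What remains is that {20a} does speak: it attaches the significance label to secondary results without limit, and the tests it prescribes make no joint use of the repeated measurements or of the pre-operative values already collected.

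Three stronger readings are tempting, and the article does not support them:

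- A reader might infer that every secondary outcome will be tested at every visit. Section {12} says when data are collected and {20a} says which test suits which data type. Neither says that each visit or each SF-12 component gets its own test.
- A reader might infer that the chance of a false secondary benefit is at least 27%. That value is for nine tests at an assumed correlation of 0.5 and counts false harm as well as false benefit. For benefit alone it is 13%, and higher correlation lowers both figures, so 27% is not a floor.
- A reader might take the entry under {20b} as proof that the matter is handled nowhere. That entry concerns additional analyses such as subgroups and has no bearing on secondary multiplicity.

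**Conclusion.** The concern holds in a limited form. Section {20a} gives primary and secondary results the same significance label, over a set of about nine scheduled secondary comparisons. If each is tested separately and nothing differs between the arms, at least one will be called significant with probability of about 20% to 37% in either direction, or about 10% to 20% in favour of the plaster. Those figures rest on three things the article does not settle: separate tests at each visit, the count of nine (at least two serum measures, one VAS score per visit), and correlations between 0.7 and 0. At a correlation of 0.9 they fall to 12% and 6%, still above the nominal 5% and 2.5%.

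This is a matter of labelling and of a better use of the data. The multiplicity of secondary tests leaves the confirmatory primary test and the data collection untouched. It is a cheap improvement, not a fault that undermines the trial.

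**What to change.** Amend {20a}, and the analysis plan to match, as follows:

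1. Apply the p ≤ 0.05 significance label to the primary outcome only.
2. For VAS severity and for each SF-12 component, estimate one between-arm difference over the post-operative visits from a repeated-measures model adjusted for the pre-operative value.
3. Compare the 24 h serum measures between arms with adjustment for their pre-operative value.
4. State that secondary results are supportive and are reported as estimates with 95% confidence intervals, without a claim of significance.

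Optionally, if a confirmatory secondary claim is wanted, name one key secondary outcome and test it only after the primary is significant.

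The cost is a change of wording and slightly more analysis work. No new data or patients are needed, because all pre-operative and post-operative values are already scheduled. The price is that isolated secondary p values can no longer be called significant.

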#### Interim analyses {21b}

Not an applicant.

## Methods for additional analyses (e.g., subgroup analyses) {20b}

Not an applicant.

### Methods in analysis to handle protocol non-adherence and any statistical methods to handle missing data {20c}

Sensitivity analysis was used for the lost causes, and the results of the last observation carried forward or the baseline observation carried forward were used for the sensitivity analysis of the measurement data. The sensitivity analysis of the counting data includes the analysis of the cases in the experimental group and the control group as the ineffective treatment and the best/worst case. In the worst-case analysis, the control group was treated successfully and the experimental group was treated as a failure.

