##### Experimental group

The patients in the experimental group will receive a 2-day AHP plus conventional Torasetron hydrochloride therapy. Treatment procedures in sequential order are to locate the acupoints, disinfect the skin, and attach the plaster on the skin over the acupoints. It must be removed immediately if an allergic reaction occurs, which may be described by patients as a burning sensation, severe itchiness, blisters, pruritus, or rash on the local skin. A total of 2 sessions will be performed 24 h and 48 h after the operation. The treatment starts before anesthesia before the operation, with at most 6 h of treatment twice per day.

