### Criteria for discontinuing or modifying allocated interventions {11b}

The trial can be stopped in case of other diseases or aggravation during the trial.The trial can be stopped in case of emergency or serious adverse events.If the patient withdraws from the trial or fails to continue the trial, or fails to cooperate with the treatment, the trial can be stopped.During the period of patients participating in the trial, the occurrence of infection affects the data of this trial, and the trial can be stopped.

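### Carrying the pre-operative VAS score forward gives dropouts a presumably nausea-free result, so it does not stress-test post-operative severity

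*Protocol article*

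**What the plan says.** The section on statistical methods {20a} names multiple imputation for missing values ("The missing values will be implemented by the method of multiple imputations") and an intention-to-treat analysis. The section on non-adherence and missing data {20c} then adds sensitivity analyses of two kinds.

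- Continuous data: "the results of the last observation carried forward or the baseline observation carried forward were used for the sensitivity analysis of the measurement data". It does not say which rule applies to which variable.
- Categorical data: "the analysis of the cases in the experimental group and the control group as the ineffective treatment and the best/worst case". The worst case is defined against the herbal plaster (AHP): "In the worst-case analysis, the control group was treated successfully and the experimental group was treated as a failure".

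On severity, the Outcomes section says: "The severity will be self-assessed using the scores from the visual analog scale (VAS) at pre-operation, postoperative 8 h, 24 h, and 48 h". The scale runs from 0 (none) to 10 (severe). SF-12 is measured before the operation and at 24 h and 48 h; serology before the operation and once after it, at 24 h. The Experimental group section starts treatment before anesthesia. The sample size section allows for 20% dropout and sets 83 patients per group.

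**The concern.** BOCF is usually defended as cautious because, in a treatment trial, baseline is the ill state: a dropout is credited with no improvement. Here the order is reversed. The baseline score comes before the anesthetic and the surgery that cause PONV, so carrying it forward credits the dropout with never having had the symptom.

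The same section scores a missing patient as a failure when the variable is categorical. One dropout could thus be a treatment failure in one sensitivity analysis and nausea-free in another, although both are meant to probe the same multiple-imputation result.

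If more patients were lost from the AHP arm, BOCF would move the VAS comparison in favour of AHP and appear to confirm a benefit that came from the missing data.

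**Working it through.** **Inputs from the protocol article.** 83 per arm; two-sided 5% level; VAS 0 to 10 with 0 = none; VAS before the operation and at 8, 24 and 48 h; 20% dropout with no split by arm. The article gives no figure for the effect of the imputation rule, so there is nothing to reproduce first.

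**Assumptions, not in the article.** Post-operative VAS mean m = 3 and SD s = 2 in both arms (no true effect); pre-operative VAS = 0; dropout unrelated to the score; unequal splits of 25%/15% and 30%/10% (AHP/placebo) for illustration.

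**Step 1: what each rule imputes for VAS.**

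| Last VAS observed | BOCF imputes | LOCF imputes |
|---|---|---|
| Pre-operative only | pre-operative score | pre-operative score |
| 8 h | pre-operative score | 8 h score |
| 24 h | pre-operative score | 24 h score |

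BOCF always reaches back past the operation. LOCF does so only when no post-operative score exists.

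**Step 2: mean and variance under BOCF.** With dropout d and baseline 0:
- mean = (1 − d)m
- variance = (1 − d)(s² + m²) − [(1 − d)m]²

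*20% vs 20%.* Means 2.40 and 2.40; difference 0; rejection 5%.

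*25% vs 15%.*
- Means 0.75 × 3 = 2.25 and 0.85 × 3 = 2.55; difference −0.30.
- Variances 0.75 × 13 − 2.25² = 4.69 and 0.85 × 13 − 2.55² = 4.55.
- SE = √[(4.69 + 4.55)/83] = 0.334; ratio 0.30/0.334 = 0.90.
- Rejection = Φ(0.90 − 1.96) + Φ(−0.90 − 1.96) ≈ 0.147.

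*30% vs 10%.*
- Means 2.10 and 2.70; difference −0.60.
- Variances 0.70 × 13 − 2.10² = 4.69 and 0.90 × 13 − 2.70² = 4.41.
- SE = √[(4.69 + 4.41)/83] = 0.331; ratio 1.81.
- Rejection ≈ Φ(1.81 − 1.96) ≈ 0.44.

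**Step 3: simulation.** 20,000 trials per setting, t test, scores limited to the range 0 to 10.

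| Dropout AHP / placebo | BOCF: difference, rejection | LOCF, a quarter of dropouts with no post-operative score | LOCF, all dropouts with a post-operative score |
|---|---|---|---|
| 20% / 20% | 0.00, 5.1% | 0.00, 5.1% | 0.00, 5.1% |
| 25% / 15% | −0.31, 16.0% | −0.08, 5.9% | 0.00, 5.2% |
| 30% / 10% | −0.62, 48.2% | −0.15, 8.1% | 0.00, 5.2% |

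The last column takes the carried score as equal to the final score. A separate run of 5,000 trials gave 15.1% and 48.8% for the two unequal BOCF splits. The formula's 44% is lower because it does not limit scores to 0 to 10, which reduces the spread. With unequal dropout, almost all BOCF rejections favour AHP.

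**Step 4: the other continuous variables.** Serology has one post-operative sample, so if it is missing both rules impute no change from before surgery; the article gives no favourable direction for that. For SF-12, nothing says that the pre-operative score of a patient awaiting lumbar fusion is a best score.

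**The case against.** The case on the other side is substantial.

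- **LOCF is mostly a different rule.** A reader might infer that both rules impute the symptom-free state. They do not: from 8 h onward LOCF carries a real post-operative score, and Step 3 shows no bias in that case. The article also joins the two rules by "or", so BOCF need not be used for VAS. This stands and limits the point to BOCF, and to LOCF without any post-operative value.
- **The main question has a stress test.** A reader might infer that the primary result is left unprotected. PONV occurrence as a categorical outcome gets failure imputation and a worst case against AHP, and the sample size is framed in rates. The exposure is therefore a secondary outcome, plus PONV frequency only if it is analysed as continuous and given a pre-operative zero.
- **The error rates are conditional.** They need unequal dropout; the article's single 20% figure does not supply it. They describe one sensitivity test alone, not the trial's type I error. With equal dropout and a real benefit, BOCF would shrink the difference (by a factor of 0.8 at 20%), not inflate it.
- **Greater loss from the AHP arm is conjecture.** The instruction "It must be removed immediately if an allergic reaction occurs" concerns the plaster and does not say that assessment ends. Plaster procedures are the same in both arms, and the article reports a lower rate of adverse drug reactions with AHP. Likewise "or fails to cooperate with the treatment, the trial can be stopped" stands under criteria for discontinuing or modifying interventions; it does not say that data collection ends. But it does not say that it continues either, and the placebo carries only 5% of the original herbal concentration, so unequal loss is possible.
- **Detail may sit in an unseen analysis plan.** That would cover which rule goes with which variable. It does not cover BOCF itself, which this article names.

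**Conclusion.** The point holds for BOCF, and for LOCF in a patient with no post-operative score, applied to VAS severity; it extends to PONV frequency only if that is analysed as continuous with a pre-operative zero. For these the rule is close to a best-case imputation for the missing patient and runs against the categorical rules in the same section.

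Under the assumptions above, the spurious AHP benefit is about 0.3 points with about 15% rejection at 25% versus 15% dropout, about 0.6 points with 44–49% at 30% versus 10%, and nil (about 5%) at 20% in both arms. The VAS mean, SD, zero baseline and dropout splits are all assumed; the zero baseline is a reasonable inference, since pre-operative nausea is not described.

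The documents do not support the wider reading that SF-12, LOCF after an observed post-operative score, or the categorical PONV analysis is distorted in this way. For serology, both rules simply impute no change. What is at stake is false reassurance about a secondary efficacy outcome.

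**What to change.** 1. In {20c}, drop BOCF for post-operative VAS severity and PONV frequency, and drop LOCF for these where no post-operative value exists.
2. In their place, use a delta-adjusted (tipping-point) version of the multiple imputation already planned in {20a}: worsen the imputed post-operative values in the AHP arm by increasing amounts and report the amount at which the conclusion changes.
3. Keep the failure and worst-case analyses for categorical data as they are.
4. To match the intention-to-treat statement, say that diary and interview data are still collected to 48 h after plaster removal or non-cooperation with treatment, unless consent is withdrawn. This concerns data collection only.

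The cost is a few sentences, a few extra imputation runs, continued assessment of inpatients over the 48 h period, and possibly a less favourable sensitivity result.

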### Plans to give access to the full protocol, participant level-data, and statistical code {31c}

Not an applicant.

### Oversight and monitoring

#### Composition of the coordinating center and trial steering committee {5d}

Not an applicant. The whole trial process will be monitored by the China Academy of Chinese Medical Sciences.

#### Composition of the data monitoring committee, its role, and reporting structure {21a}

Not an applicant. The data will be monitored by an independent statistician (the Institute of Clinical Basic Medicine, China Academy of Chinese Medical Sciences, China), who is not involved in the implementation of statistical analysis of the trial.

#### Adverse event reporting and harms {22}

Adverse events (AEs) are defined as any undesirable experience participants endure during the trial period, regardless of whether or not it is associated with the intervention. The participants will be instructed to report AEs to the research team, and a research nurse will monitor participants for potential occurrences of AEs. All details of AEs, such as time of occurrence, severity, management, and causality to the intervention, will be recorded in the case report forms. All AEs will be followed up from the beginning until resolution.

Current evidence has shown that AHP has a lower rate of adverse drug reactions (ADRs) [19]. However, our trial still pays more attention to possible ADRs, particularly associated with skin lesions (urticaria and pruritus) or other symptoms during the study period.

### Frequency and plans for auditing trial conduct {23}

The management department of the research institute or members of the ethics committee will review the progress of the trial every 3 months. The process will be independent of investigators and the sponsor.

### Plans for communicating important protocol amendments to relevant parties (e.g., trial participants, ethical committees) {25}

Any protocol modification changes such as eligibility criteria, outcomes, or analyses will be notified in writing to the management department of the research institute or members of the ethics committee.

### Dissemination plans {31a}

Research Report including results data will be promoted throughout the country through academic exchanges.

## Discussion

PONV is a common and unavoidable side effect of current forms of anesthesia. It has more impact on postoperative recovery and affects various aspects of life, including physiological, social, and psychological well-being. The Anesthesia Branch of the Chinese Medical Association provides an expert consensus including pharmacological and non-pharmacologic interventions [4]. The guidance document showed TCM therapies such as acupuncture and ginger which might relieve the symptoms of PONV still be under consideration. So the use of AHP for PONV after PLIF with general anesthesia needs rigorous scientific evidence.

This study has the potential to contribute to the development of an effective intervention to relieve PONV. It will also establish feasibility and provide preliminary evidence on the efficacy and safety of AHP in PONV. Based on the results of the study, future clinical practice should fully consider alternative and complementary therapy and include long-term administration and follow-up.

